### Sample size determination

Sample size calculation was done with respect to the primary endpoint. A previously evaluated pilot study showed the following data for total training time needed to reach proficiency: mean difference between group 1 and group 2 was 15 seconds; standard deviation in group 1 was 15.6 seconds, whereas it was 22.2 seconds in group 2. This difference can be detected with a two-sided significance level *α* = 0.05 and a power of 1 − *β* = 0.8, with a group size of 27 participants randomized to each group.

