**Fig. 3 Fig3:**
[figure not shown]
Standardized silicone suture pad

Training pairs are required to rate each other throughout the training process until they reach the predefined competency levels for knot quality, suture position, and time. Procedural competency is assessed using a previously validated modified 23-point implementation checklist [14] (Table 1), originally published by Munz et al. [29].

Knot quality is scored using a 5-point scale designed by Muresan et al. [10], which assesses a knot’s throws, tightness, edge opposition, and ability to hold under tension (Table 2). Furthermore, accuracy is recorded by measuring the distance (mm) of the stitch from the edge of the entry and exit points of the standardized suture pad. Operative time is also recorded.

A trainee demonstrates competency for the C-loop upon finishing it in ≤01:15 (min:sec), attaining ≥18 points on the procedural implementation checklist, scoring ≥4 on the knot quality scale, and maintaining stitching ≤2 mm from the edge of the suture pad’s entry and exit points (Table 3). According to the available medical literature, experienced surgeons (expert level) reach these goals for the surgical C-loop [14]. Once a student has reached competency according to his or her training partner, a specially trained peer tutor is asked to provide expert assessment. If the participant then performs a C-loop, attaining the aforementioned competency criteria under supervision of the tutor, he or she is considered proficient in the technique; thus proficiency is achieved once a trainee completes the C-loop suturing technique on two consecutive occasions with the predefined competency criteria – once for the partner and once for the peer tutor assessment.

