### Primary endpoint

The primary endpoint is total training time needed to reach proficiency in a predefined standardized suturing and knot tying technique.

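### The sample-size inputs (difference 15 s, SDs 15.6 s and 22.2 s) are not plausible for total training time to proficiency; the unit or the quantity appears to be wrong

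*Protocol article*

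**What the plan says.** The Primary endpoint section reads: "The primary endpoint is total training time needed to reach proficiency in a predefined standardized suturing and knot tying technique".

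The Sample size determination section ties its inputs to that same quantity: "A previously evaluated pilot study showed the following data for total training time needed to reach proficiency". The inputs are "mean difference between group 1 and group 2 was 15 seconds; standard deviation in group 1 was 15.6 seconds", and for the other SD "whereas it was 22.2 seconds in group 2". With a "two-sided significance level *α* = 0.05 and a power of 1 − *β* = 0.8", the section arrives at 27 participants per group. It gives no pilot means and no pilot size.

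The Training curriculum section sets the scale of the endpoint. For a single knot: "A trainee demonstrates competency for the C-loop upon finishing it in ≤01:15 (min:sec"), together with the procedure, knot-quality and accuracy goals. The section describes these goals as expert level. Further, "proficiency is achieved once a trainee completes the C-loop suturing technique on two consecutive occasions", once for the partner and once for the tutor. Group 1 must reach this standard on the shoebox and then again on the box trainer. Trainees change places at least every five completed knots. Under Inclusion and exclusion criteria, students with more than 2 hours of laparoscopic course training are excluded. Under Secondary endpoints, the number of attempts is an outcome.

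**The concern.** A total accumulated over repeated attempts by novices should vary between trainees by at least the length of a few knots. The stated SDs are well below the time allowed for one competent knot. They are of the size expected for a single attempt, or for minutes labelled as seconds.

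Two things are at stake. The 15 s target difference is the benchmark against which the primary result, including a null result, will be read. This paragraph is also the only justification given for the sample size. If the figures do not describe total training time, the stated power has not been worked out for the primary endpoint.

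**Working it through.** **Inputs.** Difference 15 s, SDs 15.6 s and 22.2 s, two-sided α = 0.05, power 0.80, 27 per group (Sample size determination); two-sided t test (Statistical analysis); up to 75 s for one competent knot (Training curriculum, Table 3).

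**1. The plan's own figure.**
- Pooled SD = √((15.6² + 22.2²)/2) = √((243.36 + 492.84)/2) = √368.10 = 19.19 s.
- Standardised difference = 15/19.19 = 0.782.
- Normal approximation: n = 2 × (1.960 + 0.842)²/0.782² = 25.7, so 26 per group.
- Noncentral t: power 0.789 at 26 and 0.805 at 27 per group (0.803 at 27 with the Welch test).

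So 27 is the smallest group size that reaches 80%. The arithmetic reproduces.

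**2. The inputs against the competency rule.** Take an attempt of 75 s, the most that a competent knot may last.
- One additional knot shifts a total by 75/22.2 = 3.4 SDs in group 2 and 75/15.6 = 4.8 SDs in group 1.
- The SDs correspond to 15.6/75 = 0.21 and 22.2/75 = 0.30 of one attempt, and the target difference to 15/75 = 0.20 of one attempt.

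The article gives no typical attempt time, so a range is needed. At an assumed 60 s per attempt, one knot shifts a total by 2.7 to 3.8 SDs. At an assumed 180 s it is 8.1 to 11.5 SDs.

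**3. What the SDs would require.** Suppose every attempt takes 75 s and only the number of attempts varies, by at most one knot. The variance of the count is then p(1 − p), where p is the share of trainees needing the extra knot.
- Group 1: (15.6/75)² = 0.043, so p is between 4% and 5%, about 1 trainee in 27.
- Group 2: (22.2/75)² = 0.088, so p is about 10%.

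Almost every trainee would have to need the same number of attempts. That does not sit with novices training to an expert-level goal, or with the number of attempts as an endpoint.

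**4. Consequence under each explanation.**
- *Wrong unit, for example minutes.* The standardised difference has no unit: 15/19.19 = 0.782 again, and power at 27 per group stays 0.805. The target difference would be 15 min, 60 times the printed one.
- *Another quantity, for example time per knot.* Power for total time is then unknown, because no SD of total time is available. Two assumed SDs, equal in both groups, show the scale. With an SD of 75 s, power for a 15 s difference at 27 per group is 11%, and 393 per group would be needed for 80%. With an SD of 10 min, the difference detectable at 80% power is (1.960 + 0.842) × 10 × √(2/27) = 7.6 min.

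**The case against.** The best defence is that the section labels its figures as total training time, in the same terms as the primary endpoint, and that nothing in the text says they are per-knot times. If the slip is only seconds for minutes, the sample size, the test and the power are unaffected. This stands, and it limits the consequence: power is in doubt only if the figures are not total time.

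Four stronger readings are tempting but not supported:
- *The figures are impossible.* The article gives no pilot mean, attempt count or novice time per attempt, so there is no direct check. The five-knot rule limits the length of a turn and does not say how many attempts are needed. Implausible under the article's own rules is as far as the text goes.
- *Group 1's two compulsory extra competent knots, up to 2 × 75 = 150 s, contradict a 15 s difference.* The 15 s is a net difference. Time spent on the shoebox may be recovered on the box trainer, which is the trial's hypothesis. An upper bound on one component says nothing about the net mean.
- *The coefficient of variation is absurdly small.* Any such value needs an assumed number and length of attempts that the article does not supply. The argument rests on the SDs relative to one knot.
- *The trial is underpowered.* The low-power figures above depend on assumed SDs and on the other-quantity explanation. They illustrate what is unknown and are not estimates.

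**Conclusion.** The concern holds as a mismatch between the sample-size inputs and the endpoint. It is not an arithmetic error. The stated SDs are about 0.2 to 0.3 of one 75 s attempt, so a single additional knot would move a trainee's total by roughly 3 to 5 SDs. Either the unit or the quantity is almost certainly wrong, and only the pilot data can show which. This rests on the 75 s competency limit as a yardstick for one attempt, and on trainees differing in how many attempts they need. As printed, the paragraph should not stand, because its target difference and SDs are figures that the trial relies on. Whether 27 per group is enough remains open: about 80% power stands if only the unit is wrong, and is not established for total training time if the figures describe something else.

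**What to change.** Check the three figures against the pilot data, then do one of the following in Sample size determination:

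- **If the unit is wrong:** correct it for the difference and both SDs, and state the target difference in the right unit. The 27 per group and about 80% power remain.
- **If the figures describe another quantity:** replace them with the pilot mean difference and SDs of total training time, counted over all attempts and, for group 1, both stages. Then restate the power, or the difference detectable at 80% power, that 27 per group give. Enrolment is left as it is.

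In either case, give the pilot group means and pilot size so that a reader can check the scale.

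The cost is one look-up and a rewritten paragraph. The downside is that, in the second case, the stated power or detectable difference may become less favourable.

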### Ethical and legal aspects

All data for the study is recorded anonymously, treated confidentially, and is evaluated by authorized staff for scientific purposes only. Participants’ names are kept separate from all study data and are not used for the study. Each participant is assigned a designated code that is used for the entire study documentation and data collection. This study is offered in addition to compulsory university courses. Participation in this study is voluntary and may be ended at any time. There are no foreseeable negative consequences related to participation. The participating staff of the Heidelberg MIS training center is experienced in the handling of training devices and in tutoring MIS. The benefits of training for students are numerous: stamina, concentration, and manual adroitness are enhanced and practiced, surgical interest may be sparked or strengthened, and students receive practical laparoscopy experience, which may be used during later work. In the event that a participant’s physical or mental health becomes jeopardized due to participation in the present study, the participant will be withdrawn immediately and excluded from the study. Written informed consent is obtained from each trainee. Ethical approval was obtained from the Ethics Committee of the Medical Faculty at Heidelberg University prior to the beginning of the study (Code S-334/2011). The Consolidated Standards of Reporting Trials (CONSORT) guidelines for randomized controlled trials and Standard Protocol Items: Recommendations for Interventional Trials (SPIRIT) guidelines for implementation of study protocols were followed [34, 35]. This trial was registered with the German Clinical Trials Register (DRKS) in Freiburg, Germany on 12 August 2015 with the trial registration number DRKS00008668.

## Discussion

This study aims to assess the differences in the learning of the psychomotor and visuospatial aspects of laparoscopic suturing and knot tying between those who learn them sequentially and those who learn them simultaneously. Trainees typically learn these aspects simultaneously, but no support was found necessitating this methodology. We expect that trainees who start on the shoebox will learn the C-loop much quicker than those who begin with the box trainer. However, it remains to be determined whether these skills quickly transfer to the box trainer with laparoscopic view. Nonetheless, it is important to ascertain which training method will be the most efficient for training centers. The potential for shorter learning curves and more effective use of resources, e.g., training center space, time, and trainers is rationale in itself to explore alternatives to current standards. The results of this study have the potential to shift the current paradigm for the training of laparoscopic suturing and knot tying or strengthen the present standard.

### Trial status

Recruitment started in April 2015 and is expected to finish by December 2015.

## Consent

Written informed consent was received from the participants for publication of this manuscript and accompanying images. A copy of the written consent is available for review by the editor-in-chief of this journal.

## Abbreviations

ICC: intraclass correlation coefficient
LC: laparoscopic cholecystectomy
MIS: minimally invasive surgery
OR: operating room
VR: virtual reality
